### Eligibility criteria

#### Inclusion criteria

The inclusion criteria are as follows: (1) patients may be of either sex; (2) patients must have good general health; (3) patients must be without teeth in both arches, users of upper and lower conventional complete prostheses, or, necessarily, users of a complete upper prosthesis (although edentulous mandibular) in good condition [28]; (4) prosthesis must be made from thermally polymerized acrylic resin and acrylic teeth; (5) patients must present with DS types IB, II, or III, according to the Newton Modified Classification [10]; and (6) their prostheses should present with biofilm with a score equal to, or greater than 1, according to Additive Index Exclusion criteria.

The following patients will be excluded: those patients who (1) present with prostheses with adaptation problems, failures, repairs, or fractures; (2) have allergy to any of the products studied; (3) have severe/serious illness that requires frequent hospitalization; (4) have systemic conditions favorable to the development of *Candida* spp.; (5) have used antibiotic, anti-inflammatory, or antifungal agents in the 4 weeks prior to the study; (6) have other lesions on the oral mucosa; (7) are already practicing palatal mucous brushing at recruitment; and (8) use replacement prostheses during the experimental period.

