The risk of adverse effects is low, although the use of palatal brushing may promote trauma in the case of excessive force. If the patient has a complaint about the products under investigation or adverse events, they may interrupt the treatment at any time, and notify us of what has happened. To verify if the patient is performing the protocol and minimizing any risks, there will be a consultation 5 days after the beginning of the treatment, for clarification of doubts and follow up. We expect good adherence due to the provision of an effective treatment modality as a major benefit combined with the need for routine clinical attendance at the School of Dentistry of Ribeirão Preto, and the fact that the provision will be made for post-trial care. We will also remind participants by telephone a few days before each follow-up appointment.

The patients will be instructed to avoid the consumption of beverages or foods that alter the metabolism, such as coffee, soda, alcohol, and chocolate, and to avoid physical exercise 24 h before the tests.

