### Study outcomes

#### Primary: denture-related stomatitis remission

To evaluate the effect of the hygiene protocols on DS remission, the participants will be examined under the baseline condition and also 10 days after starting their specific use of the protocol. To quantify the inflammation, standardized photographs of the palate will be obtained (Digital Camera, Canon EOS, Canon EF 100 mm/2: 8 Macro Lens and Canon ML3 Circular Flash), with the focus centered on the median raphe region. The images will be transferred to the computer and two blinded, previously trained researchers will assign scores according to the classification of Kabawat et al. [10].

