### Statistical analysis

Data entry and analysis will be conducted in a blinded fashion. The data collected for the groups, prior to adherence to the hygiene protocols, such as age, gender, and grade of schooling, will be compared to ascertain initial similarity. The effect of groups on primary and secondary outcomes will be assessed. When applicable (i.e OHIP-EDENT), pre-treatment values will be applied as a co-variable in the statistical model. The significance level of the tests will be 0.05. Noncompliant participants will be followed up, such as those requiring interruption of one of the hygiene protocols, and to evaluate the significance of protocol deviations. In other words, the statistical analysis will consider the participants according to the treatment received (per protocol), as well as according to the planned treatment (intention to treat (ITT)); the results will be compared.

The data will be analyzed for homogeneity; in the case of non-normal distribution, the Brunner Langer nonparametric test will be used. For the categorical variables (questionnaire) the Friedman test will be applied to compare the different time points, and the Kruskal-Wallis test will be applied to compare the groups. Correlation between the quality of life indices and the quantitative variables will be tested (Pearson correlation coefficient). The Tukey test with Bonferroni adjustment will be used for subgroup analysis. The Dunn post-test test will be used with the Kruskal-Wallis test.

A flowchart of the participants will be prepared for a detailed explanation of the characteristics of the sample and the quantification of quitters and missing participants. This part will provide the number of individuals examined, reasons for exclusion, and the number of recruited, treatment-allocated participants who complete the trial and are included in analysis at the study end. The flowchart will provide the reasons for any deviation from the protocol.

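### The analysis labelled per protocol groups participants by treatment received, which is as-treated; separately, exclusion 8 describes a post-allocation event and would conflict with ITT if used to remove randomised patients

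*Protocol article*

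**What the plan says.** Three places in the protocol article bear on who is analysed, and in which arm.

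- **Statistical analysis, the two analyses.** The article states that "the statistical analysis will consider the participants according to the treatment received (per protocol), as well as according to the planned treatment". The sentence continues "according to the planned treatment (intention to treat (ITT)); the results will be compared". Just before it, the section says "Noncompliant participants will be followed up, such as those requiring interruption of one of the hygiene protocols", the aim being to judge how much protocol deviations matter.
- **Statistical analysis, the flowchart.** It will report, among other counts, the "treatment-allocated participants who complete the trial and are included in analysis at the study end".
- **Eligibility criteria.** The exclusion list opens with "The following patients will be excluded: those patients who" and its last item is "8) use replacement prostheses during the experimental period". No separate rule is given for events after allocation.

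Planned interventions sets out four arms of 25. Groups 3 and 4 share the immersion product and differ in what is used to brush the palate: a soft brush alone in Group 3, the product with a soft brush in Group 4. The general instruction to all patients is to brush the palate with water. Patients with a complaint or an adverse event are told that "they may interrupt the treatment at any time". For the primary outcome, "the participants will be examined under the baseline condition and also 10 days after starting their specific use of the protocol".

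**The concern.** The words in parentheses and the rule in front of them do not match. Analysis by treatment received assigns each person to an arm according to what they did. Per protocol leaves each person in the arm to which they were randomised and omits those who deviated. The two analyses can contain different people in different arms, and they answer different questions.

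The design gives the distinction practical force. A Group 4 patient who keeps brushing the palate but leaves out the product has in effect received Group 3. Under the literal rule that patient is counted in Group 3. If people who drop the product also tend to do worse, prognosis is carried from one arm to the other and appears as a treatment difference.

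Exclusion 8 raises a separate question. The other exclusions describe a patient's state or history at entry. This one describes something done during the experimental period, which follows allocation. If it is acted on, a randomised patient leaves the study for later behaviour, whereas ITT would keep that patient in the assigned arm.

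**Working it through.** **1. Label against rule.** The protocol article contrasts treatment received with planned treatment. The second is ITT by assigned arm. The first is its as-treated counterpart, because it regroups people. Nothing in the sentence restricts the set to adherent patients in their own arm, which is what per protocol means.

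**2. What the literal rule could do.** The plan gives no figure here to reproduce, so this is an illustration under assumptions:

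- 25 patients per arm (Planned interventions).
- No true difference; both arm means are 0 as randomised, and a higher score is worse.
- *k* Group 4 patients keep brushing the palate without the product and are counted in Group 3. The values of *k* are assumed.
- These patients do worse than adherers by D (assumed; no value is given in the document).

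For the Group 4 mean to be 0, non-adherers must sit at (1 − k/25)D and adherers at −(k/25)D. Check for k = 5: 0.2 × 0.8D + 0.8 × (−0.2D) = 0.

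After the move:

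- Group 4 mean = −(k/25)D, with n = 25 − k.
- Group 3 mean = k(1 − k/25)D / (25 + k), with n = 25 + k.
- Difference = 2k/(25 + k) × D.

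| k | Group 4 | Group 3 | False difference | ITT |
|---|---|---|---|---|
| 1 | −0.04D | 0.96D/26 = +0.037D | 2/26 = 0.077D | 0 |
| 3 | −0.12D | 2.64D/28 = +0.094D | 6/28 = 0.214D | 0 |
| 5 | −0.20D | 4D/30 = +0.133D | 10/30 = 0.333D | 0 |

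For comparison, leaving the same *k* patients out of Group 4 without moving them gives a difference of (k/25)D: 0.04D, 0.12D and 0.20D. A correctly defined per-protocol analysis is therefore not free of selection either, which is why it should serve only as a sensitivity analysis.

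**3. Exclusion 8 against ITT.** Side by side, one section excludes patients for an act during the experimental period, and another analyses patients by planned treatment. Both can hold only if the exclusion does not remove randomised patients from the ITT set. The article does not say so, and its flowchart wording can be read as completers only.

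For scale, assume a true remission rate of 30% to 50% in both arms and removal of non-remitters from one arm of 25 only. These are assumptions, and this is the unfavourable case. Expected remitters are 7.5 or 12.5.

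- 1 removed: 7.5/24 = 31.2% or 12.5/24 = 52.1%, a rise of 1.3 to 2.1 points.
- 2 removed: 7.5/23 = 32.6% or 12.5/23 = 54.3%, a rise of 2.6 to 4.3 points.
- 4 removed: 7.5/21 = 35.7% or 12.5/21 = 59.5%, a rise of 5.7 to 9.5 points.

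**The case against.** The strongest reply is that ITT is planned in the same sentence and non-compliers are followed up, which is what ITT needs. A second analysis beside it, whatever its name, cannot damage it. This stands. A reader might infer that both features break the randomised comparison, and the document does not support that. The as-treated analysis leaves ITT untouched; only exclusion 8 could affect it, and only if applied after allocation.

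It can also be said that nobody is explicitly moved between arms, and that the authors may loosely mean those who received their assigned protocol. That is possible, and the authors' own label favours it. But the rule as written says otherwise, and an analyst following it would regroup patients.

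The example from Group 4 to Group 3 holds only for a patient who keeps brushing without the product. One who stops palate brushing altogether has received none of the four arms. The permission to interrupt treatment concerns stopping, not switching, so it is no evidence that such crossing will be common. The article expects good adherence, with a consultation at day 5, telephone reminders and a primary assessment at 10 days. This argues for the lower end of the range.

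On exclusion 8, a planned replacement could be asked about at entry, and the article does not state that randomised patients are dropped from analysis. The conflict with ITT is therefore conditional.

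Finally, a reader might conclude that the trial has no stated answer because neither analysis is called primary. An article may leave that ranking to an analysis plan that is not shown, so the silence is not a fault in itself.

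**Conclusion.** The point holds in a limited form. The article defines its per-protocol analysis by an as-treated rule, so the planned comparison with ITT is not the check it is called. Under the stated assumptions the distortion is about 0.08D for one patient moved and 0.33D for five. It is confined to the second analysis and rests on an unknown D, on assumed numbers of patients, and on all of them continuing to brush without the product.

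Exclusion 8 is worded as an event after allocation and conflicts with ITT if it is used to remove randomised patients. The document implies that use but does not spell it out. Apart from that condition, the planned ITT comparison is intact. These are stated rules that need correcting; they do not call for a redesign.

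**What to change.** - **Per protocol.** Define it as participants analysed in their randomised arm without major deviation, and delete the reference to treatment received. Alternatively, rename the existing analysis as-treated and treat it as exploratory.
- **Role of each analysis.** State that ITT by assigned arm carries the conclusion and that per protocol is a sensitivity analysis. If the full analysis plan already says so, align the article's wording with it.
- **Exclusion 8.** Take it out of the eligibility list. Record use of a replacement prosthesis as a protocol deviation, with the patient kept in ITT and left out of per protocol.

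The cost is wording. It needs no new data provided that anyone who met exclusion 8 was still assessed at day 10; if not, those patients are missing data in ITT and should be reported as such. The Trial status section says clinical results are already being analysed and that the cytokine and MUC1 analyses are still to start, so the change should be dated and made without reference to results by arm.

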### Planned interventions

All patients will receive verbal and written instructions according to the hygiene protocols: they should brush the palate region with a soft toothbrush and water for 2 min, once a day (Toothbrush CS 5460C Adulto Ultra Macia, Curaprox, Curaden Swiss do Brasil Imp. Exp. LTDA, São Caetano do Sul, São Paulo, Brasil); immerse their dentures in the specific product once a day for the length of time proposed by the manufacturer; and brush the prosthesis for 2 min using a specific brush (Prosthesis Brush BDC150/152/153, Curaprox, Curaden Swiss do Brasil Imp. Exp. LTDA, São Caetano do Sul, São Paulo, Brazil) and neutral soap, three times a day. In addition, all patients will be instructed to remove the prosthesis during the night and leave it in a container with clean water, and in the morning to rinse the prosthesis under running water before inserting it into the oral cavity. Neutral soap and the solutions will be available to participants in identical dosing vials and in sufficient quantity for continuous use for 10 days; for greater control and monitoring of the hygiene protocol. citric acid in the form of an effervescent tablet will be removed from the package and placed in neutral packaging.

The parallel groups as determined by the different hygiene protocols will each consist of 25 participants. The protocols are as follows:
Group 1 (G1 (control group)) - brushing the palate with a soft brush and prosthesis immersion in 0.25% sodium hypochlorite solution (control group)Group 2 (G2) - brushing the palate with a soft brush and prosthesis immersion in 0.15% triclosan solutionGroup 3 (G3) - brushing the palate with a soft brush and prosthesis immersion in citric acid (Nitradine, Bonyf AG, Liechtenstein, Switzerland)Group 4 (G4) - prosthesis immersion and brushing of the palate with citric acid and a soft brush (Nitradine, Bonyf AG, Liechtenstein, Switzerland)

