### Sample size estimation

Sample size for the quantitative outcomes was determined based on the primary outcome of this study (denture-related stomatitis remission). According to a previous trial [11], we used standard deviation of 2.19 (group 1 - saline group) and 1.79 (group 2 - sodium hypochlorite), a 95% confidence interval (bilateral), and a detectable difference of at least 2 logs. Based on power of 80%, this clinical study requires at least 21 participants. An additional 20% will be added to the planned sample to compensate for possible dropouts, thus resulting in a total of 25 participants.

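### Adding a Bonferroni correction to Tukey's test is redundant if, as seems likely, both cover the pairwise comparisons between the four arms; the cost is power only, and its size depends on an unstated divisor

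*Protocol article*

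**What the plan says.** The Statistical analysis section sets a single level for all tests: "The significance level of the tests will be 0.05". It then gives the post hoc procedure: "The Tukey test with Bonferroni adjustment will be used for subgroup analysis". The sentence after that assigns Dunn's procedure to follow Kruskal-Wallis. The section does not say which comparisons the Bonferroni step covers, how many there are or what the divisor is. No subgroup is defined anywhere in the article.

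On the design, Planned interventions states: "The parallel groups as determined by the different hygiene protocols will each consist of 25 participants". There are four such groups, allocated in equal proportions.

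The Sample size estimation section is a two-group calculation with SDs of 2.19 and 1.79, a two-sided 95% level and "a detectable difference of at least 2 logs". Its result is: "Based on power of 80%, this clinical study requires at least 21 participants". It mentions no allowance for multiple comparisons.

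**The concern.** Tukey's test is itself a multiplicity procedure. Its critical value comes from the studentized range, so the chance of any false positive among all pairwise comparisons of the arms is held at 0.05. Bonferroni applied to those same comparisons corrects a family that is already controlled.

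The subgroup label obscures what the sentence is for. The Dunn sentence beside it is a post-test for comparing groups, and the Tukey sentence reads as its parametric counterpart. The trial's stated hypothesis is that the protocols do not differ, which also calls for comparisons between arms.

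What is at stake is power. With 25 patients per arm, an unnecessarily strict threshold makes a real difference between hygiene protocols easier to miss. The article intends its results as guidance for practice, where a missed difference may be taken to mean that the protocols are interchangeable.

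**Working it through.** **Inputs.** Four arms of 25 (Planned interventions); two-sided 0.05 and 80% power; difference δ = 2 logs; SDs 2.19 and 1.79 (Sample size estimation). Combined SD: √[(2.19² + 1.79²)/2] = √[(4.7961 + 3.2041)/2] = 2.00. Four arms give 4 × 3/2 = 6 pairs; this six is derived and is not stated in the article.

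**The plan's own figure.** n per group = 2(1.960 + 0.842)² × 2.00²/2² = 15.7, so 16, or 17 by the t test. The stated 21 does not follow from the stated inputs. The dropout step does: 21 × 1.2 = 25.2, given as 25. The mismatch at 21 is a separate matter and does not affect this point. Power is therefore computed at 25 and 21 per arm directly.

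**Method.** One pairwise comparison in a four-arm layout with pooled error, df = 4(n − 1). Noncentrality = δ/(SD√(2/n)): 2/(2√(2/25)) = 3.54 at n = 25, and 2/(2√(2/21)) = 3.24 at n = 21. Critical |t| is:
- Tukey: q(1 − α; 4, df)/√2 with α = 0.05.
- Tukey followed by Bonferroni with divisor m: the same with α = 0.05/m.
- Bonferroni alone over six pairs: the two-sided t quantile at 0.05/6.

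Power comes from the noncentral t distribution.

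| Procedure | Critical t, n = 25 | Power, n = 25 | Critical t, n = 21 | Power, n = 21 |
|---|---|---|---|---|
| No adjustment | 1.985 | 93.8% | 1.990 | 89.3% |
| Tukey | 2.615 | 81.9% | 2.624 | 73.0% |
| Bonferroni alone, six pairs | 2.694 | 79.8% | 2.705 | 70.2% |
| Tukey, then divisor 2 | 2.878 | 74.2% | 2.891 | 63.7% |
| Tukey, then divisor 3 | 3.023 | 69.5% | 3.037 | 58.2% |
| Tukey, then divisor 6 | 3.257 | 61.0% | 3.275 | 49.1% |

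**Loss against Tukey at n = 25.** 81.9 − 79.8 = 2.1 points for Bonferroni alone; 7.7 points with divisor 2; 12.4 with divisor 3; 20.9 with divisor 6. At n = 21 with divisor 6 it is 73.0 − 49.1 = 23.9 points.

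**Error rates with divisor 6.** Family-wise error is 0.05/6 = 0.0083 instead of 0.05. The per-comparison level at n = 25 falls from 0.0104 to 0.0016.

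**Sample size for 80% power.** Tukey alone needs 25 per arm, which is the planned number. Tukey with divisor 6 needs 34.

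**Other true differences, n = 25, divisor 6.** The loss is 24.3 points at 1.75 logs, 9.0 at 2.5 logs and 1.9 at 3 logs.

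**The case against.** The strongest reply is that the double correction of six comparisons is a reading and is not stated. The authors may have used the phrase loosely for Bonferroni-adjusted pairwise tests, and then only about 2 points are lost. This stands: a reader might infer that the plan gives up some 20 points of power, but the text does not fix the divisor, so that figure is only the top of the range at 25 per arm.

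Bonferroni might instead have been meant across outcomes or time points, which Tukey does not cover. That would not be redundant, but nothing in the Statistical analysis section says so. It is a reason to word the fix so that it bars only a second correction of the same comparisons.

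A genuine subgroup analysis might be described in a fuller document. A reader might infer that no such analysis exists; a condensed article supports only that none is defined here. If subgroups were meant, the double correction of the arm comparisons would not be shown. The article would then name no parametric post-test for its main question, so the sentence would still need attention.

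The power figures may also not carry over to the primary outcome. Stomatitis remission is scored on a classification from photographs, and the plan sends non-normal data to a nonparametric method, so Tukey may never be used on it. This stands.

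Finally, the error is conservative, and false positives are not inflated. This also stands, and it limits how serious the point is.

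**Conclusion.** The point holds in limited form. On the likely reading, the sentence adds to Tukey's test a correction that its family-wise control makes unnecessary, under a label the article does not define. The only effect is lost power.

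For a normally distributed log-scale outcome at a 2-log difference, SD 2.0 and all 25 per arm retained, Tukey alone gives 82%. The literal sentence gives 74%, 70% or 61% for divisors of two, three or six. Bonferroni-only tests would give 80%. Every figure below 80% rests on an assumed divisor.

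Two further inferences are not supported. One is that the whole gap below the 0.05 level comes from the double correction: Tukey alone already tests each pair at about 0.0104, and that part is the legitimate price of six comparisons. The other is that the primary analysis has been shown to be underpowered for this reason: the calculation does not apply demonstrably to the stomatitis score.

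The sentence should be corrected, because as it stands it permits power anywhere from about 61% to 80% for the same comparison.

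**What to change.** Replace the sentence with wording such as:

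> Pairwise comparisons between the four groups will use Tukey's test (Tukey-Kramer where group sizes differ), with family-wise error held at 0.05 for each outcome and no further correction of the same comparisons.

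This also removes the subgroup label. The sentence on Dunn's procedure can stay as it is. If Bonferroni was meant for something other than the arm comparisons, say so in a separate sentence that names the family and the divisor.

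The text change is one sentence and needs no new data. The family-wise error over the six comparisons remains 0.05. The cost is that the new threshold is less strict than the literal text, and Trial status reports that clinical results are already being analysed. The change should therefore be dated and made before allocation is revealed. The Ethical considerations section also requires the research ethics committee's opinion before any protocol change.
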